## Abstract

**Introduction:**

Unplanned pregnancy remains a critical public health issue in Brazil that affects up to 65% of women in some regions and increases the incidence of both unsafe abortions and maternal mortality. Although the copper intrauterine device (IUD) is a highly effective, long-acting contraceptive method, its rate of use remains low in Brazil (only 4.4% of women of reproductive age). One of the primary barriers is the pain experienced during placement of the device, which discourages adherence. Although multiple social and cultural determinants influence IUD uptake, insertion-related pain constitutes a modifiable, procedure-specific factor that may directly affect both pain perception and anticipatory discomfort. Conventional pain management strategies, such as anti-inflammatories and local anesthetics, have produced inconsistent results. Photobiomodulation (PBM) is a non-invasive therapy with anti-inflammatory and analgesic properties that has shown promise in managing pelvic pain in contexts such as labor.

**Methods and analysis:**

The proposed randomized, double-blind clinical trial will investigate the effectiveness of PBM at reducing pain during the placement of the copper T 380 IUD. Seventy-two women will be randomly allocated to either an active PBM group (n = 36) or sham PBM control group (n = 36). In all participants, the standard IUD placement protocol will follow the guidelines of the Brazilian Ministry of Health. Pain will be assessed using the Visual Analog Scale (VAS) at multiple time points: during each step of insertion (Pozzi clamp, hysterometry, IUD placement) as well as 5 min, 15 min, 24 hours, and 48 hours post-procedure. The secondary outcomes will be analgesic use, anxiety levels (GAD-7), quality of life (WHOQOL-100), satisfaction with the procedure, and adverse effects. Ethics and dissemination. This clinical trial received approval from the Research Ethics Committee of the Mandaqui Hospital Complex (process: 7.367.867) and was registered in ClinicalTrials.gov (NCT06984796). Statistical analyses will be conducted using SPSS v24.0, with a significance level of 5%. Either parametric or nonparametric tests will be applied, depending on the data distribution. Kaplan-Meier curves will be used to assess time to pain resolution. The results will be disseminated through peer-reviewed publications.

## Introduction

Unplanned pregnancy affects up to 65% of women in some areas of Brazil, increasing the risk of unsafe abortions and inadequate prenatal care, which significantly contribute to maternal mortality. Ensuring access to long-acting contraceptive methods, such as the copper intrauterine device (IUD), is crucial in reproductive planning [1,2]. Despite its effectiveness, only 4.4% of women use an IUD, with many opting for birth control pills or sterilization [3]. The IUD is suitable for most women of reproductive age, including adolescents, and is also indicated for emergency contraception and controlling heavy uterine bleeding [4].

Despite these benefits, pain during placement causes fear and reluctance among patients and constitutes a significant barrier to IUD adoption [5,6]. While broader social and cultural determinants influence IUD uptake, insertion-related pain is an immediate, modifiable procedural factor that may directly affect both pain perception and anticipatory fear. Visceral pain arises from cervical dilation, with afferent nerves transmitting impulses via the T10-L1 dermatomes [7], while somatic pain results from pelvic floor distension, involving the S2-S4 dermatomes [8]. Evidence of adequate pain control remains inconclusive, as studies involving the use of non-steroidal anti-inflammatory drugs (NSAIDs), local anesthetics, and cervical preparation methods have demonstrated limited effectiveness [2,5–7]. A Cochrane review found that 2% lidocaine gel, misoprostol, and most NSAIDs failed to reduce pain during IUD placement, with only some formulations of lidocaine, tramadol, and naproxen having effects in specific groups [6].

Given the lack of effective pharmacological interventions, alternative approaches have been explored. Paravertebral blockade between T10 and S4 has shown promise for analgesia during labor [2,5,9], while transcutaneous electrical nerve stimulation (TENS) has been effective at controlling pelvic pain [10,11]. Photobiomodulation (PBM) has demonstrated analgesic effects for lower back pain [12,13] and labor pain [9], suggesting the potential to reduce discomfort during IUD placement [14]. As the Brazilian Ministry of Health does not currently recommend analgesic measures for IUD placement, further studies are needed to assess the effectiveness of PBM at improving patient comfort and increasing adherence to this contraceptive method, ultimately benefiting public health [4]. Our experimental hypothesis is that the use of PBM can reduce pain perception during the placement of the T 380 copper IUD for contraception.

Therefore, the aim of this study is to propose a protocol for the assessment of whether preventive photobiomodulation (PBM) alters pain perception during the placement of the T 380 copper intrauterine device (IUD) for contraception in women without comorbidities.

## Materials and methods

A single-center, randomized, double-blind, controlled clinical trial with two parallel groups, designed as a superiority trial, will be conducted following the schedule of enrollment (Fig 1) and SPIRIT Statement (https://www.spirit-statement.org/) (S1 File).

**Fig 1 pone.0349031.g001:**
[figure not shown]
Template illustrating recommended content for schedule of enrollment, interventions, and assessments.

The study protocol (original language S2 File; in English S3 File) received approval from the Research Ethics Committee of the Mandaqui Hospital Complex in São Paulo, Brazil (7.367.867). The original document (S4 File) and a translation (S5 File) were presented Any unforeseen events or modifications during the study will be reported to the ethics committee and disclosed in future publications. After the main investigator provides a verbal and written explanation of the study, individuals who agree to participate will sign an informed consent form. Participants who wish to receive the study results will provide their email addresses and the full article will be shared upon publication. The participants will be involved in the development of the study design and the execution of the trial but not involved in the data analysis or reporting.

Treatment will be performed at the Mandaqui Hospital Complex in the northern region of São Paulo, Brazil. The main investigator is a gynecologist with more than 10 years of experience and will perform the procedures. According to the ClinicalTrials.gov record (NCT06984796) (S6 File), the study is currently listed as “Not yet recruiting”, with an anticipated starting date of March 30, 2026, and a primary completion date of May 30, 2027. The study was registered in ClinicalTrials.gov (NCT 06984796) and is in accordance with the SPIRIT 2025 Guidelines Checklist Statement.

### Calibration/Training

A single examiner will assess five women who will not be included in the study. These women will undergo clinical pain assessments identical to those proposed for the trial.

The main investigator will perform all IUD placement procedures and postprocedural assessment. This investigator will also undergo specific training for the following outcomes: anxiety, using the Generalized Anxiety Disorder 7 (GAD-7) questionnaire; quality of life, using the WHOQOL-Pain instrument; and patient satisfaction, using a questionnaire based on the method proposed by Lopes *et al.* (2015) [6].

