### Blinding (Masking)

Only the researcher in charge of administering the treatment (who opens the randomization envelopes) will be aware of the assigned intervention for each participant. The participants will be blinded because of the visual similarity of the treatments (LED on versus LED off). The researcher collecting the outcome data will also be blinded to the interventions and will not be present in the room during treatment. Group allocation will be disclosed only after the statistical analysis is completed, ensuring that the data collector and statistician remain blinded. Unblinding during the trial is not planned, as no adverse events are expected with PBM use.

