Patient satisfaction with T 380 copper IUD placement for contraception will be assessed 15 minutes after the procedure using guiding questions [6]. The assessment will include whether the placement experience was unpleasant, whether the patient would undergo the procedure again, and whether she would recommend it to a friend.

*Secondary outcome – Time required to relieve abdominal discomfort following PBM*: The time required to relieve abdominal discomfort following PBM will be recorded in hours, measured from the onset of cramps until complete pain resolution.

*Secondary outcome – Verification for IUD placement success*: IUD placement will be assessed as a binary outcome (success/failure).

*Secondary outcome – Adverse effects (uterine perforation, IUD displacement, abdominal pain, increased vaginal bleeding, and allergy)*: An open-ended question will be asked to elicit the patient’s free responses regarding adverse effects. The responses will then be listed nominally so that the patient may recall any impact that she may have forgotten to report.

*Secondary outcome – Side effects (cramps, mild pain, mild bleeding, tongue anesthesia)*: An open-ended question will be asked to enable the patient to freely describe any side effects. Effects will then be listed by name to help the patient recall any impact that she may have forgotten to report.

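### The gynecologist who inserts the IUD is also assigned the 15-minute satisfaction questions about that insertion, so courtesy answers may flatter satisfaction in both arms and attenuate the difference between them

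*Protocol article*

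**What the plan says.** Three parts of the protocol article bear on this.

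- **Who inserts.** Materials and methods: "The main investigator is a gynecologist with more than 10 years of experience and will perform the procedures".
- **Who assesses.** Calibration/Training: "The main investigator will perform all IUD placement procedures and postprocedural assessment". It then lists the instruments this person is trained for: "This investigator will also undergo specific training for the following outcomes: anxiety, using the Generalized Anxiety Disorder 7 (GAD-7) questionnaire", followed by the WHOQOL-Pain and the patient satisfaction questionnaire.
- **What is asked, and when.** Secondary outcomes: satisfaction "will be assessed 15 minutes after the procedure using guiding questions", covering "whether the placement experience was unpleasant, whether the patient would undergo the procedure again, and whether she would recommend it to a friend". The outcome list calls these items closed-ended.

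The Blinding section adds a safeguard on allocation: "The researcher collecting the outcome data will also be blinded to the interventions and will not be present in the room during treatment".

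**The concern.** The satisfaction items ask the woman to judge a procedure. The person assigned to collect the answers has just performed it. Some women who found it unpleasant, or who would not repeat or recommend it, may soften the answer out of courtesy.

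Two things are at stake for this secondary outcome. The reported satisfaction proportions may be too favourable in both arms. A real difference between active and sham photobiomodulation (PBM) may also look smaller in absolute terms than it is. The items matter to the trial's rationale, because the Introduction presents insertion pain as a barrier to IUD adoption, and willingness to repeat or recommend lies close to that question.

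**Working it through.** **Reading the passages together.** Materials and methods and Calibration/Training place insertion and post-procedural assessment with one person. The training list shows that this assessment includes satisfaction. The article calls the GAD-7 a self-report instrument and has participants mark the VAS. For satisfaction it speaks only of a questionnaire, closed-ended items and guiding questions, with no mention of self-completion. The Blinding section keeps the outcome collector unaware of the arm. That protects against an assessor who treats the arms differently. It does nothing about a woman's reluctance to criticise the operator.

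**Illustration of size.** The documents give no expected satisfaction rate and no rate of courtesy answers, so every rate below is an assumption. Only n = 36 per arm comes from the protocol.

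Let p_S and p_A be the true proportions in the sham and active arms who found the placement unpleasant. Let c be the share of those women, equal in both arms, who do not say so, and assume no misreporting in the other direction. Then:

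- observed proportions: p_S(1 − c) and p_A(1 − c)
- observed difference: (p_S − p_A)(1 − c)

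With 70% versus 40% and c = 25%: 0.70 × 0.75 = 0.525, 0.40 × 0.75 = 0.30, difference 0.225 instead of 0.30.

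The relative measure depends on which answer is counted. The ratio of 'unpleasant' answers is unchanged: 0.70/0.40 = 1.75 and 0.525/0.30 = 1.75. The ratio of favourable answers does shrink: 0.60/0.30 = 2.00 becomes 0.70/0.475 = 1.47.

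Power of a two-sided 5% comparison of two proportions, normal approximation, with d the observed difference and p̄ the mean of the two observed proportions:

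power = Φ{[d − 1.96·√(2p̄(1 − p̄)/n)] / √([p₁(1 − p₁) + p₂(1 − p₂)]/n)}

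For 60% versus 30% at c = 20%, the observed rates are 0.48 and 0.24, so d = 0.24 and p̄ = 0.36. The terms are 1.96 × √0.0128 = 0.2218 and √0.0120 = 0.1095. This gives Φ(0.167) = 56.6%.

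| c | Observed difference (points) | Power, 70 v 40 | Power, 60 v 30 | Power, 50 v 20 |
|---|---|---|---|---|
| 0% | 30 | 73.5% | 73.5% | 77.2% |
| 10% | 27 | 63.5% | 65.1% | 70.2% |
| 20% | 24 | 53.7% | 56.6% | 62.5% |
| 30% | 21 | 44.7% | 48.3% | 54.6% |
| 50% | 15 | 29.4% | 32.9% | 38.6% |

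Equal suppression shrinks the difference in proportion. It does not erase or reverse it.

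**The case against.** **The article does not say that the questions are asked aloud.** The woman might already fill in a form, and the full protocol, which is not shown, might say so. This is a fair limit: face-to-face questioning is inferred, not stated. The assignment and the training are stated, however, and nothing in the article separates the operator from the answers. The Blinding section does not name its outcome collector, so it does not displace that assignment.

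**The mechanism works alike in both arms.** This stands. The assessor is described as blinded and serves both arms, so the point gives no reason to expect a result tilted towards either one. The trial was also sized on eight pain measurements, not on satisfaction, so the power figures above describe no promise that the plan makes.

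**Stronger readings that a reader might infer.**

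- *That the operator also asks about harms at 15 minutes.* The article says "An open-ended question will be asked to elicit the patient’s free responses regarding adverse effects", followed by a prompted list, but gives no interviewer and no time point. Harms are not in the training list, and they include IUD displacement and increased bleeding, which fit poorly with a 15-minute interview. The prompted list also partly counters under-reporting. The documents do not support this reading.
- *That differences between arms will be hidden.* No courtesy rate is given, and even the assumed model only shrinks a difference.
- *That the woman must grade how unpleasant it was.* The text asks only whether it was.

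**Conclusion.** The point holds as a modest weakness in how one secondary outcome is collected. The plan assigns the satisfaction questionnaire to the operator whose procedure is being judged and does not say that the woman completes it alone. Courtesy answers may make satisfaction look too favourable in both arms and may attenuate the absolute difference.

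The size cannot be derived from the documents. The factor (1 − c) rests on an equal courtesy rate in both arms and on no misreporting the other way; the table shows the range under those assumptions. Neither arm is favoured, and the point makes no claim about the primary pain outcome or about harms. It calls for a cheap improvement and leaves the validity of the main comparison untouched.

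**What to change.** Amend Calibration/Training and the patient satisfaction paragraph under Secondary outcomes to say that, 15 minutes after the procedure, the woman completes the closed-ended satisfaction items herself, out of the operator's sight. The form carries only her study ID and goes into a sealed sleeve that the operator does not open.

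Leave the collection of adverse and side effects in its stated order, open question first and list second. A self-completed form that showed the list at once would undo that order, so the new form should hold the satisfaction items only.

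The cost is a form layout, a supply of sleeves and a sentence in each of the two places. The article lists the trial as not yet recruiting, so the change can be made before the first participant. The small downside is that some women may need reading help. It should come from a team member who neither inserted the IUD nor knows the allocation. That excludes the researcher who applies PBM, because under the Blinding section "Only the researcher in charge of administering the treatment (who opens the randomization envelopes) will be aware of the assigned intervention for each participant".

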### Sample size calculation

The total sample size will be 72 participants. This number was calculated to provide an 80% power (α = 0.05) with an effect size of 0.14. The number of patients per group was determined using a sample size calculation with G*Power 3.1.9.7. The sample was calculated for two groups, and 8 measurements will be performed: at baseline, during the IUD insertion phases (Pozzi, hysterometry, and IUD placement), at 5 and 15 minutes after placement, and at 24 and 48 hours after the procedure.

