### Allocation (Sequence generation, allocation concealment mechanism, implementation)

A random sequence generator available online (https://www.sealedenvelope.com/) will be used to select the block randomization option with two treatments at a 1:1 ratio, resulting in equal numbers of patients in each group (n = 36 per group). As the total sample size is 72 patients, 12 blocks of six patients each will be established. Opaque envelopes will be sequentially numbered (1–72) and will contain the randomized group allocation. These envelopes will be sealed and stored securely until the IUD is placed. Only the designated researcher responsible for treatment will be aware of the assigned intervention. After opening, the envelope will be resealed and stored with the patient’s medical record, remaining concealed until the final statistical analysis. An individual not directly involved in the study will generate the random sequence and prepare the envelopes.

All participants will undergo the same IUD placement protocol performed by the same healthcare provider, as described in the “IUD Placement Protocol” section. Immediately after placement, the researcher in charge of applying PBM will retrieve and open an envelope, maintain the order of the remaining envelopes, and administer the assigned treatment (active or sham PBM). Only this researcher will be aware of the allocation.

The main investigator will oversee data storage (digital platforms) and organization. The statistician will be responsible for data analysis and will remain blinded to the interventions. The envelopes will also store participant records (patient history questionnaire, demographic data, risk factors, and statement of informed consent) and will be securely archived.

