### Statistical analysis

Statistical analysis will be performed using the Statistical Package for the Social Sciences (SPSS) version 24.0 or equivalent software package. The significance level will be set at 5% (p < 0.05) for all tests. Data normality will be determined using the Shapiro-Wilk test. Continuous variables will be reported as either the mean and standard deviation or the median and interquartile range, depending on the distribution of the data. Categorical variables will be expressed as absolute and relative frequencies. For comparisons between the experimental group (active PBM) and control group (sham PBM), the Mann-Whitney test will be used for continuous variables with non-normal distribution. When the expected minimum value is less than 5, categorical variables will be compared using either the chi-square test or Fisher’s exact test. The analysis of pain-related variables (intensity measured by the Visual Analog Scale [VAS]) at different time points (baseline, during placement, 5 and 15 minutes, and 24 hours after the procedure) will be conducted using the Friedman test. As the primary outcome will be measured repeatedly over time, the analysis will account for the within-subject correlation inherent to this repeated-measures design.

For the measures of anxiety (GAD-7), quality of life (WHOQOL-100), and satisfaction with the procedure, the Mann-Whitney test will be used to compare groups across assessment time points. The use of post-procedural analgesics will be compared between groups using repeated-measures analysis of variance (ANOVA). No interim analyses or stopping guidelines are planned due to the short duration of the trial and low risk.

Missing data will be assessed for frequency and pattern. In the event of missing values, the analyses will be performed using the available data, and the extent of missingness will be reported. If necessary, appropriate statistical methods will be applied depending on the nature and proportion of the missing data.

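### The 80% power quoted for 72 women at effect size 0.14 is not the power of the tests named for the primary VAS pain outcome

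*Protocol article*

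**What the plan says.** The section Sample size calculation fixes the total: "The total sample size will be 72 participants". It then gives the basis: "This number was calculated to provide an 80% power (α = 0.05) with an effect size of 0.14". The software is named ("The number of patients per group was determined using a sample size calculation with G*Power 3.1.9.7"), and so is the layout: "The sample was calculated for two groups, and 8 measurements will be performed". The eight measurements run from baseline to 48 hours and are the same VAS readings that the Outcome variables section lists as primary, with none singled out. The test, the effect-size metric, the correlation between measurements and the sphericity correction are not given.

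The Allocation section randomises exactly the calculated number, 36 to each arm: "As the total sample size is 72 patients, 12 blocks of six patients each will be established".

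Under Statistical analysis, the comparison of VAS pain across time points "will be conducted using the Friedman test". Arms are to be compared by Mann-Whitney when a continuous variable is not normal. Repeated-measures ANOVA is named only for analgesic use. One further sentence says that the primary analysis will allow for within-woman correlation, without naming a model.

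**The concern.** A power statement describes one test. Groups, number of measurements and a small effect size entered in G*Power point to a repeated-measures F test, and the between-arm form closest to the stated N is the group-by-time interaction. That test is not named for VAS. Friedman compares time points within women and cannot compare arms. Mann-Whitney compares arms, but on one value per woman, so one time point or one summary at a time.

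This is a two-arm superiority trial, and readers will attach the 80% to active versus sham PBM on pain. If the arms are compared as the plan names it, and the true effect is f = 0.14 (0.28 SD between two arms), the trial would usually miss it. A null result could then be presented as coming from a trial with 80% power for that effect.

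**Working it through.** **Inputs.** From Sample size calculation: N = 72, power 80%, α = 0.05, effect size 0.14, k = 2 groups, m = 8 measurements. From Allocation: 36 per arm. From Statistical analysis: "The significance level will be set at 5% (p < 0.05) for all tests". Assumed because not stated: 0.14 is Cohen's f (the metric G*Power uses for repeated-measures ANOVA), and the program defaults of correlation ρ = 0.5 and epsilon ε = 1. Both ρ and ε are varied below.

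**Step 1: reproduce 72 at 80%.** For the group-by-time interaction, λ = f²·N·m·ε/(1 − ρ), with df (m − 1)ε and (N − 2)(m − 1)ε.

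- N = 72, defaults: λ = 0.0196 × 72 × 8 / 0.5 = 22.58, df 7 and 490, power 95.4%.
- N = 48: λ = 0.0196 × 48 × 8 / 0.5 = 15.05, power 81%. This is the smallest even N reaching 80%.
- The smallest even N reaching 95% is 72.

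So the stated inputs with default settings give 48, not 72. Changes that bring back 72 at about 80%:

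| Change from defaults | λ at N = 72 | Power at N = 72 |
|---|---|---|
| ρ = 0.23 | 14.66 | 80.3% |
| ε = 0.523 | 11.81 | 80.0% |
| m = 4 instead of 8 | 11.29 | 80.7% |

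The first two use inputs the article does not state. The third contradicts the eight measurements it does state.

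**Step 2: power for active versus sham PBM at 72, same f.**

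Single time point: with two equal arms d = 2f = 0.28. The t-test noncentrality is 0.28 × √(36/2) = 1.19 on 70 df, so power is 21.6%.

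Mean of eight scores (between-group effect): λ = f²·N·m/(1 + (m − 1)ρ), df 1 and 70. The numerator is 0.0196 × 72 × 8 = 11.29.

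| ρ | λ | Power |
|---|---|---|
| 0.23 | 11.29 / 2.61 = 4.33 | 54% |
| 0.3 | 11.29 / 3.1 = 3.64 | 47% |
| 0.5 | 11.29 / 4.5 = 2.51 | 35% |
| 0.7 | 11.29 / 5.9 = 1.91 | 28% |

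At ρ = 0.5 this test needs 228 women for 80%. At the ρ that rescues 72 for the interaction (about 0.23), it still has only about 54%.

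**Step 3: the other reading of 0.14.** As partial eta-squared, f = √(0.14/0.86) = 0.403. Power at 72 is then 92% at a single time point and 99% for the mean of eight scores at ρ = 0.5. The N needed for 80% would be 52 (single time point), 30 (mean of eight) or 8 (interaction), so this reading does not give 72 either.

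**Step 4: what 36 per arm can detect.** Two-sample t test, two-sided 5%, 80% power: d = 0.67. With an assumed 10% loss, 36 × 0.9 = 32.4, taken as 32 per arm, d = 0.71. For Mann-Whitney on roughly normal data both are slightly larger.

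**The case against.** Four points can be made for the protocol, and each narrows the concern.

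First, a reader might infer that the sample size was miscalculated. That is not shown. A correlation near 0.23 or an epsilon near 0.52 gives 72 at 80%, and marked non-sphericity is plausible for readings taken minutes apart and then at 24 and 48 hours. The article refers to a fuller protocol, not seen here, which may hold these inputs. Their absence from the article is not the point.

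Second, a reader might infer that the trial is underpowered, with 22% to 35% power. That range needs 0.14 to be Cohen's f and either a single time point or a correlation of about 0.5. If 0.14 were partial eta-squared, power would exceed 90%.

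Third, the group-by-time interaction is itself a contrast of active with sham PBM. With baseline among the eight readings it is a natural place for a treatment effect to appear, and at defaults it has ample power at 72.

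Fourth, it would be too much to say that the figure fits no test in the plan, because repeated-measures ANOVA is planned for analgesic use. For VAS, the sentence on within-woman correlation leaves an interaction test open and does not exclude it.

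What these points do not answer is that the tests actually named for VAS are Friedman and Mann-Whitney, and the quoted 80% belongs to neither.

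**Conclusion.** The point holds in a limited form. The 80% for 72 women at effect size 0.14 is not tied to a named test of the primary outcome. The interaction F test can give 72 at 80%, but only with inputs that are unstated or that contradict the eight measurements.

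If 0.14 is Cohen's f, the between-arm comparison has about 22% power at one time point and, for the mean of eight scores, about 35% at correlation 0.5, rising to 54% at 0.23. The documents do not settle the metric or the correlation, so they support neither a claim of arithmetic error nor an unconditional claim of low power. This should be fixed, and easily can be while the trial is listed as not yet recruiting. It does not call for a larger trial.

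**What to change.** Keep 72 and restate the figure for the comparison that will be made, in one of two ways.

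(a) If the primary comparison is between arms at one VAS time point, replace the present claim with: 36 per arm gives 80% power (two-sided 5%) to detect about 0.67 SD, or about 0.71 SD with an assumed 10% loss. Say that this is a t-test approximation and slightly optimistic for Mann-Whitney. Name the time point, because the Outcome variables section does not.

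(b) If the interaction is intended, label 0.14 as a group-by-time effect f, give the correlation and epsilon used and the power recomputed from them, and name that interaction test as the VAS analysis in place of Friedman.

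Neither route adds participants. Route (a) costs one rewritten paragraph plus the choice of a time point, and the stated sensitivity becomes less favourable. Route (b) also changes the sentence that names the VAS test.
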